### TB preventive treatment

Standard regimens for TPT include short-course rifamycin-based options such as 4 months of daily rifampin (4R) or 3 months of daily isoniazid plus rifampin (3HR) [4]. For individuals at increased risk of drug–drug interactions or adverse events, 9 months of daily isoniazid monotherapy (9H) may be considered as an alternative. If treatment with 9H must be discontinued due to hepatotoxicity or other contraindications, 6 months of isoniazid monotherapy (6H) can be used as a secondary option.

### Outcome measures

The primary outcome is adverse events leading to permanent discontinuation of any drugs in the TPT regimen. This outcome will be defined as any clinical or laboratory event occurring during TPT that results in permanent discontinuation of one or more drugs in the prescribed regimen. For example, in patients receiving a 3HR regimen, discontinuation of rifampicin due to adverse events while continuing isoniazid to complete TPT will be considered as meeting the primary outcome.

The secondary outcomes are completion of TPT, the cascade of care for TPT, and the preventive effectiveness of TPT. TPT completion will be defined as completion of the prescribed TPT regimen within the recommended treatment period according to national guidelines. TPT cascade of care will be described by evaluating the proportions of individuals who are eligible for TPT, initiate treatment, and successfully complete treatment. The preventive effectiveness of TPT will be evaluated the incidence of progression to active TB during the follow-up period.

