**Outcomes:**

The primary outcome is the occurrence of adverse events during TPT. Secondary outcomes include TPT completion rates, predictors of non-initiation and discontinuation, and progression to active TB.

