Building a prospective cohort to collect clinical information on LTBI‑positive individuals is needed to establish a research platform for answering these questions. In this manuscript, we provide an overview of the design, methods and scope of this cohort study. This Safety of Preventive Treatment in People at Risk for Tuberculosis (STEP-TB) study is supported by the Korea National Institute of Health as a national research project. The study findings and datasets will be used as scientific evidence for developing the national TB control master plan in accordance with the TB Prevention Act. We aim to provide evidence to inform national TB policy by evaluating the safety of TPT in the high‑risk groups for active TB disease.

Among the medical high-risk groups for TB, including individuals with chronic kidney disease (CKD), chronic lung disease, diabetes mellitus, malignancy, immunosuppressive conditions, and occupational exposure, the safety of TB preventive treatment remains an important clinical concern. CKD is of special interest because patients with CKD have an increased risk of TB and may be more vulnerable to drug-related adverse events. This study aims to evaluate the safety of TPT in individuals at high risk of developing active TB disease in Korea using a multicenter prospective cohort design. The primary objective is to specifically investigate whether CKD is associated with an increased risk of adverse events during TPT. The secondary objective is to assess the association between CKD and TPT completion, to describe the TPT cascade of care among individuals at high risk of TB, and to evaluate the preventive effectiveness of TPT in reducing progression to active TB during the follow-up period. These objectives will allow a comprehensive understanding of both the safety and effectiveness of TPT in high-risk populations.

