### Study population and analytic framework

After enrollment, all individuals referred for LTBI testing will constitute the source population of the cohort and will be described in terms of baseline characteristics (Table 2). Participants will then be followed according to their LTBI test results and subsequent treatment status (Fig 1). Individuals with negative LTBI test results will be followed to monitor progression to active TB. Among those with positive LTBI test results, participants will be categorized according to whether they receive TPT. Participants receiving TPT will be followed for both adverse events related to TPT and the development of active TB. Participants with positive test results who do not receive TPT will be followed to evaluate the incidence of active TB for comparative assessment.

**Table 2 pone.0350186.t002:** Study populations and outcomes in the cohort.

Study population	Description	Purpose of analysis	Outcomes assessed
All individuals referred for LTBI testing	High-risk population undergoing LTBI testing	Description of source population	Baseline characteristics
LTBI test negative	Participants with negative LTBI test results	Assessment of natural risk of TB among test-negative individuals	Incident active TB
LTBI test positive	Participants with positive LTBI test results	Population eligible for TPT	Stratified analyses according to TPT status
LTBI positive, TPT treated	Participants receiving tuberculosis preventive treatment	Primary safety analysis population	Adverse events related to TPT; Incident active TB
LTBI positive, TPT not treated	Participants with LTBI who do not receive TPT	Comparative assessment of TB risk	Incident active TB

LTBI, latent tuberculosis infection; TB, tuberculosis; TPT, tuberculosis preventive treatment

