### Adverse event assessment

Adverse events are defined as any undesirable and unintended signs, symptoms, or diseases temporally associated with the use of a medicinal product, regardless of causal relationship, including abnormal laboratory findings. The definition and severity grading of adverse events will follow the Common Terminology Criteria for Adverse Events (CTCAE), version 5.0.[6] At the time points specified in Table 2, clinical symptoms, blood laboratory tests, and chest radiography will be assessed. Adverse events will be recorded using the standardized adverse event reporting forms provided in the S1 Table. The reporting form captures the presence of adverse events, the reported event term coded using the MedDRA terminology, data of onset and resolution, seriousness, severity grade according to CTCAE, causality assessment with anti-TB drugs, action taken, and clinical outcome of the event. Adverse events will be evaluated in terms of their type, frequency, and severity. The clinical significance of each event will be determined by the investigator based on medical judgment and patient condition.

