### Statistical analysis

Baseline characteristics of participants undergoing LTBI testing will be summarized using means and standard deviations for normally distributed continuous variables, medians and interquartile ranges for non-normally distributed variables, and frequencies with percentages for categorical variables.

To investigate if the presence of CKD alters the risk of adverse events (present/absent) during TPT, logistic regression models will be built, initially categorizing CKD as a binary variable (present/absent) and then as a ternary variable (present severe, present and not severe, absent). The minimal sufficient adjustment set for inclusion in adjusted models will be derived from a directed acyclic graph (DAG). Potential effect modification by CKD treatment will be explored amongst individuals with CKD. All statistical analyses will be performed using R or SPSS software. Additional analyses will be considered further categorizing the outcome, e.g., on the basis of adverse event severity (ordinal logistic regression) or taking into account the association between an adverse event and the drugs in use. P-values will be corrected for multiple testing.

Assessment of the association between CKD and TPT completion will take place similarly, as will progression to active TB, albeit here using time-to-event models. Finally, the cascade of care analysis will be descriptive.

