### Sample size calculation

CKD was defined according to the Kidney Disease: Improving Global Outcomes (KDIGO) guidelines as an estimated glomerular filtration rate (eGFR) <60 mL/min/1.73 m² for at least 3 months or evidence of kidney damage.[7] This study will evaluate whether CKD, a major medical high-risk condition for TB, is associated with adverse events during TPT. It is anticipated that approximately 40% of individuals undergoing LTBI testing will be LTBI-positive and initiate TPT, of whom about 15% will have CKD. Assuming adverse event rates of 20% in the CKD group and 10% in the non-CKD group, a total of 548 TPT initiators will be required to detect this difference with a two-sided α of 0.05 and 80% power.

Based on an expected LTBI positivity rate of 40%, approximately 1,370 LTBI testing candidates need to be enrolled to yield a sufficient number of treatment initiators. This sample size will provide adequate statistical power to assess whether CKD is an independent risk factor for adverse events during TPT. A total target enrollment of 1,370 participants is planned, with competitive enrollment implemented across participating sites; per-site recruitment targets may be adjusted accordingly.

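### The primary outcome is stated inconsistently (adverse events that end a TPT drug, or adverse events without that condition), so neither the primary test nor the sample size is tied to one endpoint

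*Protocol article*

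**What the plan says.** All references are to the protocol article.

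- **Outcome measures** gives the only operational definition: "The primary outcome is adverse events leading to permanent discontinuation of any drugs in the TPT regimen". It adds a worked example: on the isoniazid plus rifampin regimen, stopping one drug because of adverse events while continuing the other counts as an event.
- **Abstract, Outcomes:** "The primary outcome is the occurrence of adverse events during TPT".
- **Introduction:** "The primary objective is to specifically investigate whether CKD is associated with an increased risk of adverse events during TPT".
- **Statistical analysis:** "To investigate if the presence of CKD alters the risk of adverse events (present/absent) during TPT, logistic regression models will be built".
- **Sample size calculation:** "Assuming adverse event rates of 20% in the CKD group and 10% in the non-CKD group", leading to 548 TPT initiators and 1,370 enrolled.
- **Adverse event assessment** defines adverse events as temporally associated with a medicinal product but "regardless of causal relationship, including abnormal laboratory findings".
- **Table 2**, in the row for the primary safety analysis population, lists "Adverse events related to TPT; Incident active TB".

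**The concern.** An event that makes a patient stop a drug for good is much narrower than an adverse event as the protocol defines it. One section names the narrow event as primary and another names the broad one. The objective, the model and the planning rates all lack the narrowing condition.

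Two things are at stake. First, if the text is left as it is, either endpoint could be presented as the pre-specified primary one after the data are seen. Secondly, the two endpoints answer different questions. Under the broad reading, all-cause events and abnormal laboratory findings count. Patients with CKD may have more of these for reasons unrelated to TPT, and an association with CKD would then be hard to read as a safety signal for TPT. Under the narrow reading this problem is much smaller, because an abnormal value counts only if it leads to permanent discontinuation.

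**Working it through.** **1. The statements side by side**

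| Place | Outcome as worded | Discontinuation required? |
|---|---|---|
| Outcome measures | Adverse event ending one or more TPT drugs | Yes |
| Abstract, Outcomes | Occurrence of adverse events during TPT | No |
| Introduction, primary objective | Adverse events during TPT | No |
| Statistical analysis, logistic model | Adverse events, present or absent | No |
| Sample size calculation | Adverse event rates | No |
| Table 2 | Adverse events related to TPT | No, but relatedness is |

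No sentence says that the unqualified term is shorthand for the Outcome measures endpoint. The term has its own broad definition under Adverse event assessment. Statistical analysis also suggests further splitting the outcome by severity or by association with the drugs in use. That fits a general adverse event outcome more naturally than one already limited to events that ended a drug.

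**2. The plan's own figure**

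Inputs from Sample size calculation: p1 = 0.20 (CKD), p2 = 0.10 (non-CKD), 15% with CKD, two-sided α = 0.05, power 80%. Then k = 85/15 = 5.667 and the pooled risk is p̄ = 0.15 × 0.20 + 0.85 × 0.10 = 0.115.

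Pooled two-proportion formula for the CKD group:

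n1 = [1.96·√(p̄(1−p̄)(1+1/k)) + 0.842·√(p1(1−p1) + p2(1−p2)/k)]² / (p1−p2)²
= [1.96 × 0.346 + 0.842 × 0.419]² / 0.01 ≈ 106.3

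Total = 106.3 / 0.15 ≈ 709, so the stated 548 is not reproduced. The step 548 / 0.40 = 1,370 is. This shortfall is a separate error and would exist even if the endpoint were clear.

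**3. Power at 548 if the endpoint is rarer than assumed**

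CKD group 548 × 0.15 ≈ 82; non-CKD 466.

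Power = Φ{ [ |p1−p2| − 1.96·√(p̄(1−p̄)(1/n1+1/n2)) ] / √(p1(1−p1)/n1 + p2(1−p2)/n2) }

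At 20% versus 10%: (0.100 − 0.0748) / 0.0463 = 0.545, so power is 0.707.
At 10% versus 5%: (0.050 − 0.0546) / 0.0346 = −0.133, so power is 0.447.

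The documents give no discontinuation rate. All rows below the first are assumptions that keep the risk ratio at 2.

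| CKD vs non-CKD | Expected events in 548 | Power at 548 | Initiators for 80% | Enrolment at 40% |
|---|---|---|---|---|
| 20% vs 10% (plan) | 63 | 71% | 709 | 1,773 |
| 10% vs 5% | 32 | 45% | 1,536 | 3,840 |
| 8% vs 4% | 25 | 38% | 1,950 | 4,873 |
| 6% vs 3% | 19 | 32% | 2,639 | 6,596 |

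Discontinuations caused by adverse events are a subset of adverse events, so their rate cannot exceed the rate of all adverse events. How much lower it is cannot be derived from the documents. If instead the endpoint is broad and commoner, power moves the other way: an assumed 40% versus 20% gives about 96%.

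**The case against.** The best defence is that adverse event is simply shorthand for the endpoint in Outcome measures. That section is the only operational definition, a present-or-absent outcome in the model is compatible with it, and events that end a drug can also be graded by severity. This stands in part: the words any adverse event appear nowhere in the Abstract, Statistical analysis or Sample size calculation. It does not remove the conflict, because the Abstract gives a different primary outcome outright and nothing ties the unqualified term to the narrow one. Nor is this detail left to an analysis plan, which could not conform to both statements.

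A reader might go further than the documents allow on five points:

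- **That the model certainly tests any adverse event, and the stated primary outcome has no analysis.** This is an inference; the text is ambiguous.
- **That 20% and 10% belong to the wrong endpoint.** They may have been meant as discontinuation risks.
- **That CKD will look harmful through background illness.** This is a risk only under the broad reading. Onset, causality and clinical significance are assessed, and baseline blood tests are scheduled. The absence of a rule on worsening from baseline may be settled in documents not shown.
- **That Table 4 is defective because it schedules no adverse event assessment in untreated participants.** The primary comparison is between CKD and non-CKD among people on TPT, so untreated participants lie outside it.
- **That Table 2 sets a third primary endpoint.** Its entry is a descriptive label in an overview of populations. It needs aligning, no more.

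**Conclusion.** The inconsistency is real and concerns the primary endpoint, so it must be resolved before analysis. Outcome measures and the Abstract state different primary outcomes, and the objective, the model and the planning rates lack the discontinuation condition. As written, neither the dependent variable of the primary test nor the endpoint behind the sample size is fixed.

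This conclusion rests on the text alone. Its size in power terms is illustrative. If discontinuation is primary and its risks are half the planning rates or lower, power at 548 would be about 45% or less, given a risk ratio of 2. The gap between 71% and 80% at the planned rates must not be attributed to this point. The documents do not establish that the planned model ignores the primary outcome, or that the result will be biased against CKD.

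**What to change.** 1. Use the Outcome measures endpoint (an adverse event leading to permanent discontinuation of at least one TPT drug) in identical terms in the Abstract, the primary objective in the Introduction, Statistical analysis and Sample size calculation, and align the Table 2 label.
2. Name it as the dependent variable of the primary logistic model.
3. State whether 20% and 10% are assumed discontinuation risks. If they are not, replace them. In either case restate the power at 548 initiators for that endpoint.
4. Report any adverse event and TPT-related adverse events as secondary analyses, using the causality field already on the form and counting only events that are new or worsened from the D0 baseline. Refer to D0 and not to Visit 1, which is Day 14 in the text of Study procedures but baseline in Table 3.

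**Cost:** The endpoint changes are wording. Causality and action taken are already recorded, and Table 3 schedules blood tests at D0. The downside is that the restated power may be less favourable. If realistic discontinuation risks are well below 20% and 10%, the sponsor must either enrol more than 1,370 or accept and declare the lower power.

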### Study procedures

All study procedures will be conducted as part of routine clinical care. LTBI testing will be performed using interferon-gamma release assays (IGRA), and patient management will follow the national TB guidelines according to test results.

The baseline evaluation aims to obtain a comprehensive understanding of each participant’s general health status and social background. Sociodemographic assessment will include economic status, education level, marital status, occupation, smoking and alcohol history. Clinical evaluation will cover current symptoms, medical history, comorbidities, current medications, and vital signs (e.g., blood pressure, heart rate, height, and weight). Laboratory assessment will include LTBI testing, complete blood count, blood chemistry, glycated hemoglobin, fasting glucose, HIV antibody, hepatitis B surface antigen and antibody, and hepatitis C antibody to evaluate baseline health and infection status.

To exclude active TB, additional history taking and diagnostic testing will be performed if necessary. Symptoms suggestive of active TB include persistent cough, sputum production, weight loss, and night sweats. When such symptoms are present, chest radiography will be performed as the initial evaluation. If radiographic findings are indeterminate, the attending physician may perform chest computed tomography for further clarification. Bacteriological testing will also be conducted, including acid-fast bacilli smear and culture, and nucleic acid amplification tests such as Xpert MTB/RIF assay, to confirm or rule out active TB infection.

Participants who initiate TPT will be systematically followed according to the national TB treatment guidelines. The schedule of visits is summarized in Table 3. Clinical evaluations will be performed on Day 14 (Visit 1) and Day 28 (Visit 2) after treatment initiation, and subsequently followed until the end of treatment. The frequency of interim visits during therapy will be determined at the discretion of the treating physician.

**Table 3 pone.0350186.t003:** Study visit schedule and assessments during tuberculosis preventive treatment.

Visit	V0	V1	V2	V3	V4	V5
Visit name	Screening	Baseline	2 weeks	1 month	EOT	EOS
Timing		D0	W1-3	M1-2	M3-10	M11-15
Informed consent	O					
Medical history	O	O	O	O	O	O
TB preventive treatment		O	O	O	O	
Chest imaging		O			O	O
Blood tests		O	O	O	O	
Adherence assessment			O	O	O	
Adverse event assessment			O	O	O	
Blood sampling	O				O	

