CKD is an important high-risk condition that warrants inclusion in this study because it is consistently associated with a markedly increased risk of TB [12], largely driven by reactivation of latent infection rather than new exposure. As renal function declines, particularly in patients approaching or receiving dialysis, immune dysregulation substantially increases the likelihood of progression from LTBI to active TB disease, with reported TB incidence in dialysis populations far exceeding that of the general population [13]. In addition, TB in patients with CKD often presents atypically, leading to delayed diagnosis, poorer outcomes, and increased risk of transmission within dialysis units, thereby posing both individual and public health concerns [14]. Despite these risks, LTBI screening and treatment practices in CKD remain highly variable, largely due to diagnostic uncertainty and concerns about treatment-related adverse events, and robust, condition-specific safety data are lacking [15,16]. Recent reviews [17] have highlighted the urgent need for prospective evidence to better define the balance of benefit and harm of LTBI treatment in CKD populations and to support more consistent, evidence-based preventive strategies. By including patients with CKD across disease stages, the STEP-TB cohort is well positioned to address these critical evidence gaps and inform safer, more effective LTBI management in this high-risk group.

Importantly, this study is also designed to examine the cascade of care for LTBI [18,19], from diagnostic testing and treatment initiation to treatment completion, across different comorbidity groups. By systematically evaluating barriers and drop-offs at each step of the LTBI care continuum, STEP-TB will identify condition-specific hurdles faced by patients with complex medical comorbidities. Understanding these real-world challenges is essential for informing feasible and safe expansion of LTBI treatment policies, and the evidence generated by this cohort will directly support efforts to broaden preventive treatment strategies while maintaining patient safety.

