In clinical practice, concerns about adverse events often lead clinicians to defer TB preventive treatment [20], even after LTBI is diagnosed, particularly in patients with complex comorbidities. This reflects a persistent lack of condition-specific safety data for LTBI treatment. While randomized controlled trials provide rigorous safety assessments, such as RIFAKiD-TB trial [21], their restricted eligibility and controlled settings may limit generalizability to real-world practice. As a prospective observational cohort, STEP-TB complements existing evidence by including diverse high-risk populations and capturing both anticipated and unanticipated adverse events under routine clinical care. The resulting real-world safety data can inform condition-specific risk assessment, support shared decision-making, and provide essential evidence for the safe expansion of LTBI preventive treatment strategies. The availability of condition-specific, real-world safety data may also enhance patient-centered care by enabling clearer, evidence-based communication about the risks and benefits of TPT for individuals undergoing or considered for LTBI testing.

In conlcusion, The STEP-TB study is a multicenter prospective observational cohort designed to generate real-world evidence on the safety and implementation of TPT in individuals at high risk of developing active TB. By systematically evaluating adverse events, treatment initiation, and completion across diverse high-risk populations, this study aims to inform clinical practice, patient-centered decision-making, and national TB control policies, thereby supporting the safe expansion of LTBI treatment strategies and contributing to TB elimination efforts in Korea.

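### The primary outcome combines toxicity with the decision to stop a drug, so a CKD association on it cannot by itself be read as more or less toxicity, and the Abstract and the model describe a different outcome

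*Protocol article*

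**What the plan says.** The Introduction sets the question: "The primary objective is to specifically investigate whether CKD is associated with an increased risk of adverse events during TPT". Outcome measures answers it with a narrower event: "The primary outcome is adverse events leading to permanent discontinuation of any drugs in the TPT regimen". The working definition there is "any clinical or laboratory event occurring during TPT that results in permanent discontinuation of one or more drugs in the prescribed regimen". It names no CTCAE grade, laboratory limit or causality requirement.

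Two other places describe the outcome differently. The Outcomes paragraph of the Abstract gives it as adverse events occurring during TPT, and Statistical analysis models adverse events as present or absent. Neither mentions discontinuation.

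On setting, Study procedures states: "All study procedures will be conducted as part of routine clinical care". CKD is one of the eligibility conditions in Table 1, so the treating team knows it. Adverse event assessment says that grade, seriousness, causality and action taken are recorded for each event, and that events will be evaluated by type, frequency and severity. For the CKD comparison, however, severity appears only tentatively: "Additional analyses will be considered further categorizing the outcome, e.g., on the basis of adverse event severity".

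**The concern.** The Discussion says that "concerns about adverse events often lead clinicians to defer TB preventive treatment" and that screening and treatment practice in CKD varies, "largely due to diagnostic uncertainty and concerns about treatment-related adverse events". The study is meant to show whether such concern is justified. Its primary outcome, though, registers harm only after someone has decided to stop a drug, and that decision may reflect the same concern. An event of a given grade could end treatment in a CKD patient and be managed through in a patient without CKD, or the reverse.

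The adjustment set derived from the directed acyclic graph deals with confounding. It does not correct an outcome whose recording depends on the exposure itself. At stake is the main conclusion: a difference in stopping practice could be reported as a difference in drug toxicity, or could hide one. The Abstract and the model description make this misreading more likely because they leave out the stopping condition.

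**Working it through.** **Structure.** In each group, P(outcome) = P(event) × P(permanent stop | event). The first factor is toxicity in the broad sense. The second is a decision by the clinician, the patient or both.

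**Inputs from Sample size calculation.** 548 TPT initiators, about 15% with CKD, outcome rates of 20% (CKD) and 10% (non-CKD), two-sided α of 0.05.
- CKD: 0.15 × 548 = 82.2, taken as 82. Non-CKD: 548 − 82 = 466.
- Enrolment: 548 / 0.40 = 1,370, which reproduces.
- The stated 80% power does not reproduce. The calculation below gives about 71% for 20% against 10% at these group sizes. That is a separate matter and does not affect this point.

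**Assumed inputs (the protocol gives none).** In both groups, 20% have an event that could prompt stopping, so toxicity is identical. In non-CKD half of these end a drug: 0.20 × 0.50 = 10%, the plan's own rate. In CKD the stopping fraction is varied:
- 50%: 0.20 × 0.50 = 10%
- 60%: 0.20 × 0.60 = 12%
- 75%: 0.20 × 0.75 = 15%
- 100%: 0.20 × 1.00 = 20%

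**Chance of a significant result** (unadjusted comparison, normal approximation, pooled variance under the null). With p₁ the CKD rate, p₂ = 0.10 and p̄ the pooled rate:
- SE₀ = √[p̄(1 − p̄)(1/82 + 1/466)]
- SE₁ = √[p₁(1 − p₁)/82 + p₂(1 − p₂)/466]
- P(reject) = Φ[(p₁ − p₂ − 1.96·SE₀)/SE₁] + Φ[(−(p₁ − p₂) − 1.96·SE₀)/SE₁]

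| CKD rate | Odds ratio | SE₀ | SE₁ | P(reject) |
|---|---|---|---|---|
| 10% | 1.00 | 0.0359 | 0.0359 | 5.0% |
| 12% | 1.23 | 0.0364 | 0.0385 | 10.0% |
| 15% | 1.59 | 0.0371 | 0.0418 | 29.5% |
| 20% | 2.25 | 0.0382 | 0.0463 | 70.6% |

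Worked line for 15%: (0.05 − 1.96 × 0.0371)/0.0418 = −0.54, and Φ(−0.54) is about 0.29. The other tail adds 0.002.

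**Dependence on the assumed event rate.** Only the ratio of stopping fractions matters. With event rates of 25%, 30% or 40% in both groups, stopping fractions of 40% and 80%, 33% and 67%, or 25% and 50% each give 10% against 20%. A two-fold difference in stopping thus reproduces the whole planned contrast with no difference in toxicity.

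**The three outcome descriptions.** Under these assumptions, the outcome as worded in the Abstract and Statistical analysis (any event) would be 20% in both groups, while the outcome in Outcome measures would be 10% against 12% to 20%. The two wordings can give different answers, so the conflict is one of substance.

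**The case against.** Several objections stand and limit the point.

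- A reader might infer that the protocol says clinicians stop sooner in CKD. It does not. The Discussion speaks of deferring treatment, which is about starting, and of variable practice, which has no stated direction and is attributed partly to diagnostic uncertainty. A different stopping threshold is a plausible inference only.
- A reader might infer that the bias must inflate the CKD effect. If frailer CKD patients are not started on treatment, those treated are fitter and the effect could be understated. The high TB risk in CKD could also lead clinicians to persist.
- The outcome is not purely a physician's decision. It needs an event as well as a stop, and the patient may be the one who stops.
- The sentence "The clinical significance of each event will be determined by the investigator based on medical judgment and patient condition" is a general remark on assessment. Outcome measures does not use clinical significance to decide what counts, so it cannot carry the argument.
- Harm is not measured only through stopping, since type, frequency and severity will be evaluated.
- Treatment-limiting events are a legitimate outcome. A real difference in them is a true finding on the declared outcome, and only the toxicity reading would be wrong.
- A graded outcome is imperfect too. Events count whatever their cause and include laboratory abnormalities, so it can rise in CKD from the underlying disease.

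A further objection is that supportive analyses belong in an analysis plan that is not shown. That holds for their detail. But the outcome definition, its conflict with the Abstract and the model, and the tentative status of the severity analysis are all set in this text.

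**Conclusion.** The point holds in limited form. A CKD association on the primary outcome cannot by itself be taken as more, or less, drug toxicity, because the outcome includes a stopping decision made with CKD status known and with no grade threshold. This follows from the definition and needs no assumption. The conflict between Outcome measures, the Abstract and Statistical analysis is also plain from the text.

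The size is conditional. The 10%, 30% and 71% rest on assumed stopping fractions and equal toxicity, and the last needs every such event to end a drug in CKD but only half in non-CKD. They show what could happen and do not estimate the study's false-positive rate. The text does not support a claim that the CKD result will be an artefact, or that its direction is known. The change is worth making because it alters what can be concluded and the data are already planned for collection.

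**What to change.** 1. Reconcile the Abstract, Outcome measures and Statistical analysis so that the primary model names the discontinuation outcome.
2. In Statistical analysis, replace the tentative wording with a fixed supportive analysis. It is the same CKD model, with the outcome a CTCAE v5.0 event that is new or worsened from baseline, at or above a grade fixed before analysis (for example grade 3, with grade 2 as sensitivity), whatever action was taken. Repeat it without renal-function laboratory terms, and again restricted to events assessed as related to TPT drugs, so that underlying kidney disease is not counted as toxicity.
3. Tabulate the proportion of events leading to discontinuation by CKD status within CTCAE grade.
4. Describe a CKD effect on the primary outcome as an effect on treatment-limiting events, and interpret it as toxicity only alongside items 2 and 3, without a mechanical rule.

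Cost: a little more analysis work and possibly a more guarded conclusion. The planned reporting form already captures grade, causality and action taken, so no new data or visits are needed, and analysis is not planned until October 2028. One limit remains: grade and causality are still assessed by investigators who know CKD status.
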